### STUDY OBJECTIVES

2.2

*The primary endpoint* is the *p*rogression of coronary and aortic valve calcification (quantified by the calcification volume score) as assessed by cardiac computed tomography (CT) at 24 months. The secondary objectives can be found in the Supporting Information Material.

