### Patient follow‐up

2.6

Blood collection for serum chemistry, hematology, coagulation, and batch analysis of proteins involved in the process of calcification such as MGP and Fetuin‐A are measured at 1 Week, 1, 3, 6, 9, 12, and 24 months. Echocardiography was performed at baseline, 6, 9, 12, and 24 months (evaluation by an experienced echocardiographer with at least 10 years' experience). Calcification score (coronary or valvular) as assessed by cardiac CT was measured at 12 and 24 months. To improve clinical consistency, all CT scans were evaluated in a consensus reading by an experienced radiologist and an experienced cardiologist. Measurement of changes in intima‐media thickness of carotid artery (IMT) and flow‐mediated vasodilation of brachial artery (FMD) are performed at baseline, 6, 12, and 24 months. Blood pressure was measured at 1 week and at 1, 6, 9, 12, and 24 months. Electrocardiography was performed at 12 and 24 months. Adverse Events were evaluated at 1 week, 1, 6, 9, 12, and 24 months. MACE and major and nonmajor bleedings are documented at every visit.

The study duration was approximately 6.5 years. The planned duration of study inclusion was 55 months; the follow‐up period is 24 months. According to the trial design patients were followed‐up at 1 week as well as 1, 3, 6, 9, 12, and 24 months after inclusion.

The design of the study is illustrated in Figure 1.

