### Statistical analysis

2.9

All randomized patients with OAT due to atrial fibrillation or atrial fibrillation and/or pulmonary embolism are included in the analyses. Descriptive analyses of study data include frequencies, mean, standard deviation median, minimum, maximum values, and frequencies of missing data. Furthermore, a description of the change from baseline (absolute difference and percentage change) will be given. The calcification volume score is used in the primary analysis to evaluate the treatment effect. A linear mixed‐effects model is used with treatment effect, visit, baseline measurement, and treatment‐visit interactions as fixed effects and random intercepts for participants are included. For the primary inferential analysis, the hypothesis that the treatment‐visit interaction parameters are jointly equal to zero is tested using an *F *test. Additionally, 95% confidence intervals of parameter estimates are presented. In secondary analyses, the valvular and aortic calcification endpoints are analyzed using similar mixed models as in the primary analysis. An interim analysis is planned after 12 months of follow‐up. Significance levels are adjusted using the Fleming‐Harrington‐O'Brien method. A 5% overall significance level is used in the primary analysis. All statistical analyses are conducted using SAS or SPSS.

For the calculation of sample size for detecting the difference in volume score change between the two treatment groups the standard deviation of the change in volume, score was assumed to be 234 units, based on previous data measuring volume score change over 12 months in placebo‐treated patients with asymptomatic or mildly symptomatic aortic valve calcification.^20^ Given this assumption on the variability of volume score change, a sample size of 95 per treatment group (*n* = 190 altogether) would allow a detection of 96 units difference between the treatment groups with an 80% power using a Type 1 error of 0.05.

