## RESULTS

3

In total 192 patients were recruited between 2013 and 2018. Of these, baseline data is available for 188 patients (95 in the Phenprocoumon group and 93 in the Rivaroxaban group). The median age of the patients was 72 (IQR 67–76) in the Phenprocoumon group and 68 (IQR 65–75) in the Rivaroxaban group. Within the groups, there were 73.6% and 69.9% male patients, respectively. The main indication for anticoagulation was atrial fibrillation (95.8% and 96.8%, respectively) with pulmonary embolism being the only other indication (Table 1). In total, data for 164 patients (82 patients per group [85%]) is available at 12 months follow up and for 91 patients (45 in the Rivaroxaban group [47%] and 46 [48%] in the Phenprocoumon group). We expect the results of the study to be ready for publication by the end of 2022.

**Table 1 clc23819-tbl-0001:** Characteristics of the patients at baseline (IRIVASC)

	Phenprocoumon (*N *= 95)	Rivaroxaban (*N* = 93)
Median age (IQR), year	72 (67–76)	68 (65–75)
Male, no. (%)	70 (73.6)	65 (69.9)
Diabetes mellitus, no. (%)	23 (24.7)	26 (29.2)
Smoker, no. (%)	11 (11.5)	14 (15)
Non smoker, no. (%)	39 (41)	45 (48.3)
Ex. smoker, no. (%)	42 (44.2)	28 (30.1)
Previous MI, no. (%)	25 (26.3)	26 (27.9)
Previous stroke, no. (%)	16 (16.8)	8 (8.6)
Coronary heart disease (CHD), no. (%)	51 (54.8)	54 (60.6)
Median systolic blood pressure, right (IQR), mmHg	130 (120–143,7)	135,5 (122,7–149)
Median systolic blood pressure, left (IQR), mmHg	130 (120–140)	134 (124–145)
Median total cholesterol (IQR), mg/dl	173 (149.7–204.2)	176 (142–214.5)
Median LDL‐cholesterol (IQR), mg/dl	109 (85.5–128,5)	102.5 (82–138)
Median GFR (IQR), ml/min/1.73 m^2^	65.6 (52.8—81.5)	72.3 (57.2–84.7)
Median hemoglobin (IQR), g/dl	13.9 (13.2–15.2)	14.2 (13.1–15)
Median CHA2DS2VASc score (IQR)	3 (3–4)	3 (2–4)
Indication for anticoagulation:		
1. Atrial fibrillation, no. (%)	91 (95.8)	90 (96.8)
2. Pulmonary embolism, no. (%)	4 (4.2)	3 (3.2)
Type of atrial fibrillation		
1. Paroxysmal, no. (%)	51 (56)	57 (63.3)
2. Persistent, no. (%)	15 (16.5)	14 (15.6)
3. Permanent, no. (%)	16 (17.6)	15 (16.7)
4. New onset, no. (%)	1 (1.1)	1 (1.1)
5. Not further classified, no. (%)	8 (8.8)	3 (3.3)

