### Study limitations

3.1

This study has some limitations. Owing to the different mechanism of action of both drugs, the trial is open‐label. Furthermore, to increase recruitment, the study enrolled and randomized patients currently on OAT. It could have been better to only enroll OAT naïve patients because the difference in duration of OAT therapy before randomization could become a source of bias. Finally, the study only includes patients with a baseline AS of >50 to limit the number of study patients and to detect a sufficient progression of coronary artery or aortic valve calcification within the set follow‐up period, thus potentially limiting the ability to detect smaller differences between the groups.

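### The random-intercept primary model assumes equal variance at 12 and 24 months; if variance grows with time, the 24-month standard error and confidence interval are too small

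*Protocol article*

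**What the plan says.** Section 2.9 (Statistical analysis) of the protocol article analyses the calcification volume score with a linear mixed model. Its fixed effects are treatment, visit, baseline and treatment-by-visit, and "random intercepts for participants are included". No random slope, visit-specific residual variance or robust standard error is mentioned.

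Primary inference is on the treatment-by-visit terms: the hypothesis that the "interaction parameters are jointly equal to zero is tested using an" F test. In addition, "95% confidence intervals of parameter estimates are presented".

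The endpoint in Section 2.2 is progression "as assessed by cardiac computed tomography (CT) at 24 months". Section 2.6 says that the score "as assessed by cardiac CT was measured at 12 and 24 months". With baseline as a covariate, the model therefore has two response visits.

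The only SD in the article is 234 units, for change over 12 months (Section 2.9). The Results section reports that data for 164 patients (82 per group) "is available at 12 months follow up and for 91 patients" (45 and 46 by group). No time point is printed for the 91; I read it as 24 months.

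**The concern.** A random intercept plus one residual variance is compound symmetry: the same variance at both visits and one covariance between them. The standard error of the 24-month treatment difference then rests on a variance averaged over the two visits. If patients progress at different rates, 24-month scores spread more than 12-month scores, and the average is too low for the visit that defines the endpoint. It is lower still if fewer patients contribute at 24 months than at 12.

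At stake are the coverage of the confidence interval for the 24-month difference and the type I error of any test of it. When 24-month data are incomplete, the level of the planned interaction test is affected too.

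**Working it through.** **1. The plan's own figure.** Inputs from Section 2.9: difference 96, SD 234, 80% power, type I error 0.05 (taken as two-sided). Normal formula: n = 2(1.960 + 0.842)² × 234²/96² ≈ 93.3, so 94 per group. The noncentral t gives 95 (power 80.3%; 79.9% at 94). The stated 95 per group reproduces.

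**2. Is growing variance plausible?** Treat 24-month change as the sum of two yearly changes with equal variance and correlation r. Then Var24/Var12 = 2(1 + r), which exceeds 1 whenever r > −0.5. Pure measurement noise gives r = −0.5 exactly, and independent yearly changes (r = 0) give an SD ratio of √2 = 1.41. Section 2.5 says that progression depends on baseline calcium load, which points to real differences between patients. This is indirect support; no 24-month SD is given.

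**3. Closed form, complete data.** With k = SD24/SD12, the model uses the average variance SD12²(1 + k²)/2 where the true value is k²·SD12². The ratio of model SE to true SE for the 24-month difference is √[(1 + k²)/(2k²)], and the actual type I error is about 2[1 − Φ(1.96 × ratio)].

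- k = 1.2: √(2.44/2.88) = 0.92, type I error 7.1%
- k = 1.41: √(3/4) = 0.87, 9.0%
- k = 2: √(5/8) = 0.79, 12.1%
- k = 0.8: √(1.64/1.28) = 1.13, 2.7%

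Example with SDs 234 and 331: pooled SD = √[(234² + 331²)/2] ≈ 287. With 95 per group the model SE is 287 × √(2/95) ≈ 41.6, against a true 331 × √(2/95) ≈ 48.0.

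**4. Simulation under no treatment effect.** REML random-intercept fits of the stated model, 3,000 runs per scenario. Assumptions: SD12 = 234, normal errors, correlation 0.7 to 0.97, and 24-month data missing completely at random. SE ratio means model SE divided by empirical SE for the 24-month difference.

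| SD24 (k) | 95/95 at both visits: SE ratio | 24-month type I | interaction type I | 82/82 and 46/45: SE ratio | 24-month type I | interaction type I |
|---|---|---|---|---|---|---|
| 187 (0.8) | 1.14 | 2.7% | 4.9% | 1.17 | 2.4% | 4.4% |
| 234 (1.0) | 1.00 | 4.8% | 5.4% | 1.01 | 4.5% | 5.2% |
| 281 (1.2) | 0.93 | 6.6% | 4.8% | 0.90 | 7.5% | 5.5% |
| 331 (1.41) | 0.86–0.87 | 8.8% | 5.0–5.1% | 0.81 | 11.0–11.5% | 7.3% |
| 468 (2.0) | 0.79–0.81 | 10.9–12.4% | 4.4–5.3% | 0.70–0.72 | 15.6–16.6% | 8.9–9.5% |

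For k = 1.41 (correlation 0.71) at the unequal counts, the mean model SE is 51.0 against an empirical 62.8.

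**5. Why the interaction test differs.** With two visits it is a single contrast, the 24-month minus the 12-month treatment difference. With complete data it is estimated from within-patient differences, whose variance the model estimates correctly whatever the two visit variances are (SE ratio 0.98–1.03). Patients with a 12-month record only break this: at the unequal counts the ratio is 0.97, 0.91 and 0.84–0.87 for k = 1.2, 1.41 and 2.

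**6. The alternative.** A separate simulation (2,500 runs, same counts) gave random-intercept SE ratios of 0.89, 0.79–0.82 and 0.70 for k = 1.2, 1.41 and 2. An unstructured covariance held 4.5–5.0% throughout. With equal variances the two methods agreed (5.1% and 4.5%). That unstructured fit used maximum likelihood; the REML/Kenward-Roger version with baseline-by-visit was not itself simulated.

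**The case against.** Several objections have force.

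- **Variance growth is not documented.** A reader might infer that the 24-month SE is certainly too small. The article does not support that: at equal SDs there is no bias, and at a ratio of 0.8 the error is conservative. Nor is the SE taken from the 12-month scans alone; the variance is pooled over both visits. This stands, and the point is conditional.
- **The primary test is the interaction, not the 24-month contrast.** A reader might infer that a false positive primary result becomes two to three times as likely as stated. That size applies only to the 24-month contrast, at SD ratios of about 1.4 or more with the unequal counts. The planned F test is valid with complete data and at most about twice nominal at those counts. Whether the 24-month difference is itself one of the reported parameters depends on the visit coding, which is not given.
- **The counts are soft.** The Results section speaks of data, not scans, prints no time for the 91, and was written before the final results. The complete-data figures do not depend on it.
- **The full plan may set the residual structure.** It may, and visit-specific residual variances would be compatible with the text. But the only structure the article fixes is the restrictive one.
- **Covariates.** Section 3.1 says that the "difference in duration of OAT therapy before randomization could become a source of bias", and Section 2.8 lists two scanner models, so a reader might infer that a model without prior OAT or centre is invalid. With 1:1 randomisation, leaving them out does not by itself bias the comparison. The scans are also protected by phantom calibration, common basic settings and a blinded reader.

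**Conclusion.** The point holds conditionally. As written, and with independent equal-variance residuals, the model ties the 24-month variance to the 12-month variance. For assumed SD ratios of 1.2 to 2, the SE of the 24-month difference is understated by about 7–21% with complete data (type I error 6.6–12.4%) and by about 10–30% at the unequal counts (7.5–16.6%). The planned F test is sound with complete data and runs at 5.5–9.5% at those counts.

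These figures rest on normal errors, data missing completely at random, correlations of 0.7 to 0.97 and, for the second set, reading the 91 patients as 24-month data. The case for acting is that the alternative needs no assumption about how the variance changes and costs almost nothing when the variances are equal.

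**What to change.** In Section 2.9, replace the random intercept by an unstructured 2×2 within-patient covariance for the 12- and 24-month responses, fitted by REML with Kenward-Roger degrees of freedom. Add a baseline-by-visit term, since progression that depends on baseline load need not have the same baseline slope at both visits.

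Cost: three covariance parameters instead of two, and one fixed-effect degree of freedom. It is standard mixed-model code, with no change to data collection or sample size.

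Prior-OAT status (naive or pre-existing) and centre may be added as fixed effects for precision and chance imbalance. That is optional and not needed for validity.

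### The primary F test of treatment-by-visit interaction is not a test of the 24-month endpoint, and the text leaves open which hypothesis it does test

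*Protocol article*

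**What the plan says.** - **Endpoint.** Section 2.2 (Study objectives) defines the primary endpoint as progression of "coronary and aortic valve calcification (quantified by the calcification volume score) as assessed by cardiac computed tomography (CT) at 24 months". The abstract agrees.
- **Scans.** Section 2.6 (Patient follow-up) has the calcification score "as assessed by cardiac CT was measured at 12 and 24 months", in addition to the screening scan.
- **Model.** Section 2.9 (Statistical analysis): a linear mixed-effects "model is used with treatment effect, visit, baseline measurement, and" treatment-visit "interactions as fixed effects and random intercepts for participants are included".
- **Primary test.** The hypothesis that the treatment-visit "interaction parameters are jointly equal to zero is tested using an" F test. Confidence intervals for the parameter estimates are presented in addition. No 24-month contrast is named as the primary test.
- **Sample size.** Section 2.9 sizes the trial for "detecting the difference in volume score change between the two treatment groups": SD 234, difference 96, 95 per group, 80% power, type 1 error 0.05.
- **Interim.** "An interim analysis is planned after 12 months of" follow-up, with adjusted significance levels and a 5% overall level.

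**The concern.** The endpoint and the sample size agree with each other: both concern a between-arm difference in change. The test that carries the 5% level matches neither. What it does test depends on a choice the text leaves open.

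- **Reading A, baseline only a covariate.** Responses are at 12 and 24 months, so there is one interaction parameter: the 24-month arm difference minus the 12-month arm difference. Any effect already present at 12 months goes into the treatment main effect, which is not tested.
- **Reading B, baseline also a response visit.** There are two interaction parameters, and the test asks whether the arms differ in change at either visit. Baseline would then stand on both sides of the model.

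At stake is what the trial's one confirmatory p-value means. Under A, an early and sustained effect could be reported as a negative primary result. Under either reading, a positive result need not mean that progression differs at 24 months.

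**Working it through.** **Inputs from section 2.9:** n = 95 per arm, SD of change 234, difference 96, alpha 0.05. **Assumptions:** SD 234 at both 12 and 24 months (the source is 12-month data), complete data, and a correlation ρ between the 12- and 24-month changes. The document gives no ρ. A random intercept with constant residual variance implies 0.5 for changes from baseline, and 0.5 to 0.9 is shown. Write d12 and d24 for the arm differences at the two visits.

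**1. The plan's own figure.** SE = 234 × √(2/95) = 33.95, and 96/33.95 = 2.83. The two-sided t-test has power 80.3% at 95 per arm (79.9% at 94). The stated 95 reproduces, as a simple comparison of mean change. A direct 24-month contrast therefore has 80% power whenever d24 = 96, whatever d12 is, and rejects 5% of the time when d24 = 0.

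**2. Reading A (1 df).** With complete data the test is a t-test on the 12-to-24-month change. The SD of that change is 234 × √(2(1−ρ)), and the noncentrality is (d24 − d12)/[SD × √(2/95)].

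For 48 then 96, the numerator is 48:

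| ρ | SD | SE | 48/SE | Power |
|---|---|---|---|---|
| 0.5 | 234 | 33.95 | 1.41 | 29% |
| 0.7 | 181 | 26.30 | 1.83 | 44% |
| 0.8 | 148 | 21.47 | 2.24 | 60% |
| 0.9 | 105 | 15.18 | 3.16 | 88% |

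For 96 at both visits the numerator is 0, so the rejection rate is 5% at every ρ. For 96 then 0 it is 80% at ρ = 0.5, rising to nearly 100% at 0.9.

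**3. Reading B (2 df).** Noncentrality λ = (d12² − 2ρ·d12·d24 + d24²)/[(1−ρ²) × SE²], with SE² = 234² × 2/95 = 1152.8. Denominator df = 2 × 188 = 376.

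Worked at ρ = 0.5, where the divisor is 0.75 × 1152.8 = 864.6:
- 48 then 96: λ = (2304 − 4608 + 9216)/864.6 = 8.0, power 71%.
- 96 at both: λ = 9216/864.6 = 10.7, power 84%.
- 96 then 0: λ = 9216/864.6 = 10.7, rejection 84%.

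| Pattern (d12/d24) | ρ 0.5 | ρ 0.7 | ρ 0.8 | ρ 0.9 |
|---|---|---|---|---|
| 48/96 | 71% | 75% | 81% | 94% |
| 96/96 | 84% | 79% | 76% | 74% |
| 96/0 | 84% | 95% | 99% | nearly 100% |

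Away from ρ = 0.5 these figures take the covariance of the two changes as it stands; a random-intercept model would only approximate it.

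**4. Check.** A simulation at ρ = 0.5 (5,000 runs per pattern) gave 28.8% for 48/96 and 4.7% for 96/96 under A, and 71.8% and 83.6% under B. The baseline-adjusted 24-month contrast gave about 82%.

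**5. Interim.** If the look has only 12-month scans, Reading A has one response visit and its interaction cannot be estimated. Under Reading B the baseline-to-12-month interaction can be.

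**The case against.** The strongest reply is that the wording fits Reading B better. With a single parameter there is nothing to test jointly, and the text uses the plural. Under B, power is broadly similar to the 80% the plan aims for, and for some patterns exceeds it. With baseline as the reference visit, the interaction coefficient at 24 months is the arm difference in 24-month progression, and it would be reported with its interval. This stands, except that the coefficient is not the confirmatory test, and that listing baseline as a fixed effect pulls back towards Reading A.

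A reader might infer that the trial is set to miss a real VKA effect. The document does not support that: the severe loss belongs to Reading A, and even there 48/96 has 88% power at ρ = 0.9.

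A reader might also infer an inflated type I error. That is not so either. With 96 then 0 the arms do differ in progression at 12 months, so the test's own null is false. The pattern is also extreme, since the Discussion expects VKA to accelerate calcification and suggests no reversal. It shows only that rejection and the endpoint are different things.

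Finally, one might blame the test for low power at the numbers reported in the Results (164 patients at 12 months, then 91). Those are patients with data, not counted scans, and no time point is printed for the 91. A direct 24-month contrast with 45 per arm and SD 234 would itself have only about 49% power, so that loss comes largely from attrition.

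**Conclusion.** The point holds, as a should-fix. The confirmatory test does not correspond to the stated 24-month endpoint or to the comparison that was sized, under either reading. This is a stated rule that mismatches the endpoint, not detail left to an analysis plan.

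The consequence is conditional. If baseline is only a covariate, a sustained 96-unit difference is detected at the alpha level, and linear divergence has 29% to 88% power. If baseline is also a response, power is not the problem; interpretation is, because a 12-month-only difference also rejects. The mismatch itself depends on neither ρ nor the SD. The power figures rest on both, and on complete data. The sample-size figure is correct as computed.

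**What to change.** Before any outcome data are seen by arm:

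1. Name as the primary test the model-based treatment difference in volume score at 24 months, two-sided within the 5% overall level, with its 95% confidence interval. With baseline as covariate and 12 months as reference visit, this is the treatment coefficient plus the treatment-by-24-month coefficient.
2. State that baseline is either a covariate or a response visit, not both. If it is a response, a longitudinal model with a common baseline mean in both arms serves.
3. Report the interaction test and the 12-month contrast as secondary.
4. For any interim look that uses adjusted significance levels, state a hypothesis that can be estimated from the scans available then. Whether to keep the look is a separate design choice.

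The cost is wording only. No new data or patients are needed, and on the plan's inputs 95 per arm already gives 80% power for this contrast. The timing condition matters: the trial is open-label, recruitment is complete and follow-up data exist, so the change should be dated and should record that it was made without sight of results by arm.

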**Results:**

In total 192 patients (median age 70, 72% male) were enrolled over a period of 5 years and followed up for 2 years.

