In recent years smaller prospective trials have attempted to investigate the differential effects of VKA on calcification. Win et al. found that in comparison to Rivaroxaban, a 52‐week course or warfarin increased plaque volume and calcification as measured by MultiSlice CT (MSCT).^15^ The same group showed that similar effects were obtained with apixaban after 52 weeks compared to warfarin.^16^ This may suggest that the use of a NOAC as OAT may prevent the development of coronary calcification compared to VKA, however, both studies were single centered and included less than 50 patients per group for a relatively short follow‐up period of 52 weeks. Similarly, there have been smaller studies comparing the development of valvular calcification showing a protective effect of NOAC therapy compared to VKA in murine models.^17^ A retrospective study comparing patients on VKA and NOAC also found VKA therapy to be significantly associated with faster progression rates of hemodynamic and anatomic aortic stenosis severity.^18^

In summary, there is currently some evidence from murine and smaller trials, that the use of NOACs may reduce vascular and valvular calcifications compared to VKA therapy in patients on OAT. However, most of the trials were either retrospective or included smaller numbers of patients or shorter duration of follow‐up. The influence of rivaroxaban compared to vitamin K antagonist treatment upon development of cardiovascular calcification in patients with atrial fibrillation and/or pulmonary embolism (IRIVASC) Trial is aiming to definitively answer this question by including around 200 patients followed up for 2 years.

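### The stated 80% power requires 190 analysed patients, but only 91 appear to have 24-month data, and the article neither restates the power nor lists the loss as a limitation

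*Protocol article*

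**What the plan says.** Section 2.9 (Statistical analysis) of the protocol article sizes the trial on the change in calcification volume score: "the standard deviation of the change in volume, score was assumed to be 234 units". The source of this SD is an earlier placebo group observed for one year. From this it concludes that 95 per group, 190 in all, "would allow a detection of 96 units difference between the treatment groups with an 80% power using a Type 1 error of 0.05". It mentions no allowance for loss to follow-up. The primary endpoint (section 2.2) is CT progression at 24 months, and follow-up CT is scheduled only at 12 and 24 months (section 2.6).

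Section 3 (Results) gives 192 recruited between 2013 and 2018, 188 with baseline data (95 and 93), and 164 (82 per group, 85%) with 12-month data. The same sentence continues: "is available at 12 months follow up and for 91 patients", split 45 (47%) rivaroxaban and 46 (48%) phenprocoumon, without naming the second time point.

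The abstract's Results paragraph says that the 192 "were enrolled over a period of 5 years and followed up for 2 years". Section 3.1 (Study limitations) lists the open-label design, prior anticoagulation and the Agatston threshold. It lists neither missing 24-month data nor reduced precision.

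**The concern.** The number that must be analysed was used as the number to recruit, with a margin of two patients, in a population of median age about 70 scanned over two years. The article's own counts then show a much smaller data set at the primary time point, while the 80% figure stands without qualification and the abstract implies complete two-year follow-up.

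A reader would carry the stated power over to the eventual result. A non-significant finding could then be taken as coming from a trial with an 80% chance of detecting 96 units, when on the plan's own inputs the chance is clearly lower. With roughly half of the 24-month outcomes not in hand, the mixed model's estimate would also lean more heavily on its assumptions about the missing scans than the text suggests.

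**Working it through.** **Inputs.** From section 2.9: SD 234, difference 96, power 80%, alpha 0.05, 95 per group. From section 2.1: 1:1 allocation. From section 3: 192 recruited, 188 with baseline data, 82/82 at 12 months, then 46/45. Sidedness is not stated. Two-sided testing reproduces the figure, whereas one-sided gives 74 per group, so two-sided is used. The 12/24-month correlation is not in the document and is assumed, with a range shown.

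**Step 1: reproduce the plan's figure.** n per group = 2 × (1.960 + 0.842)² × 234² / 96² = 93.3, or 94 after rounding up. With the noncentral t distribution it is 94.2, or 95. Power at 95/95 is 0.803. The stated number is therefore correct, and it counts patients analysed. No dropout inflation is contained in it.

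**Step 2: margin.** 192 − 190 = 2 patients (1%). With 188 having baseline data (95/93), and baseline a covariate in the primary model, the margin is already used: power at 95/93 is 0.799. For scale, keeping 190 evaluable at the 12-month loss of about 15% would have meant 190 / 0.85 = 224 recruited.

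**Step 3: which time point is the 91?** All the percentages fit a denominator of 96 per group: 82/96 = 85%, 45/96 = 47%, 46/96 = 48%. CT follow-up exists only at 12 and 24 months, and the 91 follows the 12-month count. The only sensible reading is 24 months: 91/192 = 47% with data and 101/192 = 53% without.

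**Step 4: power on the plan's own inputs.** For a two-group comparison of change, SE = 234 × √(1/n₁ + 1/n₂).

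| Patients analysed | SE | Power for 96 units (t) | Difference detectable with 80% power (t) |
|---|---|---|---|
| 95/95 | 33.95 | 0.803 | 95.6 |
| 82/82 | 36.54 | 0.743 | 103 |
| 46/45 | 49.06 | 0.490 | 139 |

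**Step 5: credit for 12-month data.** The planned mixed model can use 12-month scans from patients without a 24-month scan. With monotone missingness and 82 per group at 12 months, SE = 234 × √[(1 − ρ²)(1/45 + 1/46) + ρ²(2/82)]. Power is Φ(96/SE − 1.960), and the detectable difference is 2.80 × SE.

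| Assumed ρ | SE | Power | Detectable difference |
|---|---|---|---|
| 0.5 | 46.25 | 0.55 | 130 |
| 0.7 | 43.38 | 0.60 | 122 |
| 0.9 | 39.23 | 0.69 | 110 |
| 1 (limit) | 36.54 | 0.75 | 102 |

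At SD 234, no correlation restores 80%.

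**Step 6: sensitivity to the SD.** The 234 is a 12-month figure applied to a 24-month endpoint. If the 24-month SD were 300, power at 46/45 would be 0.33. An SD of about 163 would be needed for 46/45 to give 80%.

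**The case against.** **The sample-size sentence is not an arithmetic error.** It is a conditional design statement, and it reproduces. That stands. The fault is that its condition, 190 analysed, is not met by the counts in the same article and the text does not say so. The full protocol may discuss dropout, but 190 planned and 192 recruited show that none was built into the number.

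**The recomputed power is not that of the planned analysis.** This also stands. The primary test is a joint F test of treatment-by-visit interactions, whereas both the article's calculation and the one above are for a two-group contrast. The primary model also adjusts for baseline. If baseline and change correlated at 0.5 (an assumption), the residual SD would be 234 × √(1 − 0.25) = 203. Power would then be 0.61 at 46/45, and 0.67, 0.72 and 0.81 with borrowing at ρ = 0.5, 0.7 and 0.9. A larger 24-month SD pulls the other way. A reader might infer a single replacement such as 49% or 60%, but the document does not fix the inputs for one.

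**The 91 may not be final.** The article says only that data are available. Recruitment ended in 2018 with 24 months of follow-up, so the last visits were due by about 2020. It is still not stated that the remaining scans are lost. A reader might conclude that 53% of primary outcomes are permanently missing, which goes further than the text. Even with a 24-month scan for all 164, power at SD 234 is 0.74.

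**The introduction.** A reader might say that the trial has shrunk to the size of studies it criticises, since it notes that "both studies were single centered and included less than 50 patients per group". That comparison sets this trial's 24-month completers against other studies' enrolment, and the introduction also objects to their 52-week follow-up. It describes a definitive answer as an aim, not as a result. The point does not need this argument.

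**Missing-data sensitivity analyses** are ordinary analysis-plan content. That plan is not shown, so their absence from the article is no finding.

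**Conclusion.** The point holds as a mismatch between the stated power and the article's own patient counts. The 80% for 96 units depends on 190 analysed patients, and almost no loss was allowed for. On the plan's inputs, power is about 0.49 at the reported 46/45, 0.55 to 0.69 with borrowing at assumed correlations of 0.5 to 0.9, and 0.74 if all 164 reach 24 months. The matching detectable differences are about 139, 130 to 110, and 103 units.

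These figures rest on reading the 91 as the 24-month count, on SD 234 applying at 24 months, on no gain from baseline adjustment, and on a two-group contrast standing in for the joint F test. Under favourable assumptions about baseline adjustment and correlation together, power could return to about 80%, so a shortfall under every model is not shown. What is wrong as written is the unqualified 80%, the abstract's account of follow-up, and the silence in the limitations.

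**What to change.** 1. In section 3, label the 91 as the 24-month count, if that is what it is, and say whether it is final.
2. In section 2.9, state that the 80% power assumed no loss to follow-up.
3. Restate power or detectable difference for the patients actually analysed, as a range with its assumptions: the 12/24-month correlation, the 24-month SD, and the baseline adjustment. Say that it is not the power of the joint interaction F test.
4. In the abstract, give the number with 24-month data in place of the statement that all 192 were followed for two years.
5. In section 3.1, list the missing 24-month data and the reduced precision.

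The cost is a few sentences, one short recalculation and a less favourable stated power. No further enrolment and no change to the primary model are proposed.
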